### Self-report instruments – condition specific

For participants diagnosed by UAIHC with any of the identified study clinical conditions (low back pain, fibromyalgia, depression and anxiety), one or more of the following questionnaires will be added:

• Fibromyalgia Impact Questionnaire Revised - FIQR. The 21-item FIQR is a patient report of symptoms associated with fibromyalgia in three domains: physical functioning (9 items), overall impact (2 items), and symptoms (10 items) [66].

• Roland-Morris Disability Questionnaire – RMDQ. The RMDQ is a patient report of physical disability due to low back pain (Roland & Morris, 1983). The RMDQ contains 24 yes/no items focused on limitations in walking, bending over, sitting, lying down, dressing, sleeping, self-care, and daily activities.

• Patient Health Questionnaire 9 - PHQ-9. To assess clinical depression, the PHQ-9 [67,68] will be used with patients if the PHQ-2 screening score is ≥ 3.

• Generalized Anxiety Disorder 7 - GAD-7. When scores on the GAD-2 exceed the cut point of ≥ 3 on the New Patient Intake Form, the 7-item GAD-7 will be administered [69].

### Data collected from medical records

These data will be collected at 3, 6, and 12 months. A medical records abstraction form will be used to collect the following from the patient chart for the period since the last outcomes data collection point. The results of any of the following lab tests will be captured: fasting glucose, lipid panel, thyroid stimulating hormone (TSH), glycosylated hemoglobin (HbA1c), inflammatory markers (erythrocyte sedimentation rate and high-sensitivity C-reactive protein), vitamin D status, and measures of anemia (hemoglobin, hematocrit, and mean corpuscular volume). Also captured will be each patient’s diagnosis(es), systolic and diastolic blood pressure, heart and respiratory rates, weight, waist circumference, body fat composition, smoking status, and whether the patient is on hypoglycemic, dyslipidemia, or hypertension medication. Composite scores (10-year cardiovascular disease (CVD) event risk [70], 10-year CVD mortality risk [71], and metabolic syndrome diagnosis [72]) will be captured from the chart when recorded, or will be calculated. Forced vital capacity and forced expiratory volume will be captured for participants with pulmonary disease.

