### Comparison group(s)

Data from UAIHC patients will be compared, where possible, to those of patients seen in other clinics. The primary outcome, total healthcare utilization, will be obtained from healthcare claims data for patients whose employers have given access to those data. For these patients, matched comparison groups will be developed using two different matching algorithms applied to de-identified claims data for non-UAIHC patients. One will use a straight matching algorithm based on age and gender, and the other will use propensity scores to match [49]. At least one of the participating employers also has employee lab values available. Where these data are available, the same matched comparison groups will be used to compare changes in key lab values seen across groups. Finally, several of the self-report measures have national and regional comparisons available. The measures of patient experiences and patient satisfaction are drawn from the Consumer Assessment of Healthcare Providers and Systems (CAHPS) Adult Visit Survey 2.0 [50]. The CAHPS website contains data on the results of these questions nationally, by region, and by physician specialty. The results seen for UAIHC participants will be compared to those seen by all providers nationally, by all providers in the West region, and by family practice doctors nationally. The measures of diet and exercise quality come from the Center for Disease Control and Prevention’s Behavioral Risk Factor Surveillance System survey [51]. National and statewide averages are available for these items. Unfortunately, no other secondary data sources are available for comparisons. For all other outcomes, UAIHC participants will act as their own controls by comparing their outcome measures over time to baseline.

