### Data Collection

For the outcomes evaluation, data will be collected from patient charts and self-reports at four intervals—baseline (initial clinic visit), and at 3-, 6-, and 12-month follow up periods. Participants will receive a reminder email one week before each data collection due date. Baseline data will be due within one week of enrollment. In the email they will be directed to a secure website where they can access and complete the outcomes data collection instrument. If participants have not entered their data within 3 days of their due date, they will receive another reminder email, and those who have not entered their data within another 3 days of their due date will receive a call from the UA Study Coordinator. Healthcare utilization and cost data from healthcare claims will be obtained from their employer with study participant consent. These data will be collected for one year before and one year after clinic enrollment approximately 3 months after the 12-month follow up period to allow time for all incurred claims to be recorded. De-identified claims data for the comparison groups will be collected for the same period of time with “baseline” being defined by the average start date of study participants.

Because the intervention may change over time as clinic operations start up and mature [21], fidelity monitoring data will be collected monthly from study start for 6 months, then quarterly for 6 months, and then semi-annually. Patient-reported fidelity data will be gathered on a single randomly chosen day of the last week of the data collection month from all patients seen at the UAIHC clinic that day. This day will be selected by the UA research team using a simple computer generated randomization scheme and delivered to the UA Study Coordinator the week before the data collection week. A self-administered patient version of the “How is UAIHC doing?” questionnaire will be used for patients. For clinic personnel, fidelity data will be collected during the last week of each fidelity data collection month using an online self-administered practitioner and staff version of the “How is UAIHC doing?” questionnaire. Data from audits of randomly selected, de-identified patient charts and of administrative records will also be used to assess indicators of model implementation.

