The fourth and fifth analyses will be the main outcome studies. The fourth study will be a prospective cohort study of the changes in outcomes from baseline to one year for all patients in the outcomes sample. The primary outcome for this analysis will be health-related quality of life measured in three ways (SF-6D [78], and the physical and mental component summary scores, all derived from the SF-12), with the other outcomes as secondary measures. The main comparison will be baseline to 12-month outcomes and the univariate analyses will use paired *t* tests for continuous data, and use the McNemar test for frequencies [79]. The data will also be examined for patterns of change over time in key outcomes, and the determinants of those patterns, using hierarchical linear modeling (HLM) techniques [80-82]. Fidelity measures with significant changes over time will be used as covariates [24] in these models, as well as other explanatory variables such as demographics, participants’ membership level and baseline diagnoses. If participant numbers for each of the five targeted condition allow, condition-specific outcomes will be examined for each. These same analyses will be applied to other secondary outcomes such as CVD event [70] and mortality [71] risk.

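### Selective retesting of abnormal chart labs may appear as improvement in the uncontrolled paired baseline-to-12-month tests of these secondary outcomes

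*Protocol article*

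**What the plan says.** Under Data collected from medical records, an abstraction form gathers information "from the patient chart for the period since the last outcomes data collection point". For laboratory tests the wording is "The results of any of the following lab tests will be captured", followed by glucose, lipids, TSH, HbA1c, inflammatory markers, vitamin D and anemia measures. Composite scores (cardiovascular event risk, cardiovascular mortality risk, metabolic syndrome) "will be captured from the chart when recorded, or will be calculated". The article describes no blood draw scheduled by the study.

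Table 1 marks medical records data for pre/post comparison only; the control-group cell is empty. For the fourth analysis the Analysis section states: "The main comparison will be baseline to 12-month outcomes and the univariate analyses will use paired" t tests for continuous data, with the McNemar test for frequencies. Hierarchical linear modeling (HLM) is added to study patterns of change and their determinants. The same analyses extend to cardiovascular event and mortality risk. SF-12-derived quality of life is primary there; the other outcomes are secondary.

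One controlled lab analysis is planned. Where an employer supplies lab values, "the same matched comparison groups will be used to compare changes in key lab values seen across groups" (Comparison group(s)).

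The sections disagree on whether chart data include a baseline. Data collected from medical records says "These data will be collected at 3, 6, and 12 months", as does Table 1, whereas Data Collection says "data will be collected from patient charts and self-reports at four intervals—baseline (initial clinic visit), and at 3-, 6-, and 12-month follow up periods".

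**The concern.** Questionnaires go to every participant on a schedule. A chart lab value, as the text reads, exists only if the test was done in usual care, and a repeat is plausibly more likely when the earlier result was abnormal. Whether a patient enters the paired test may then depend on the baseline value of the very outcome being tested. A group selected for high first values tends to come back lower on retest even if nothing has changed.

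For labs whose abnormality lies mainly in one direction, such as glucose, HbA1c or LDL-type lipids, this bias favors the clinic. The chart analysis has no comparison group that could expose it. The Analysis section also sets changes in cost against changes in cardiovascular risk, so a distorted lab-based score could color how the economic results are read, although it would not change the cost estimate.

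**Working it through.** **Plan's own figure.** There is none for labs. The article's sample-size statement concerns total cost and does not bear on this point.

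**Inputs from the Protocol article.** Expected outcomes sample 500; paired test, baseline to 12 months; no control group for chart data.

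**Inputs assumed, because the article gives none.** Share abnormal q = 30%, all in the upper tail. Correlation between baseline and 12-month value ρ = 0.7, 0.8 or 0.9. Retest probabilities p_a (abnormal) and p_n (normal). All 500 have a baseline value. True mean change is zero.

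**Formula.** For a standardized bivariate normal value, the expected mean change among retested patients is

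Δ = -(1 - ρ)(p_a - p_n) φ(z) / [p_a q + p_n (1 - q)],

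where z is the 70th percentile of the standard normal and φ(z) = 0.348.

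**Numbers put in.**
- 50% vs 50%: p_a - p_n = 0, so Δ = 0.
- 70% vs 50%: 0.2 × 0.348 / (0.21 + 0.35) = 0.124. Times (1 - ρ): -0.037, -0.025, -0.012 SD.
- 80% vs 30%: 0.5 × 0.348 / (0.24 + 0.21) = 0.386. Times (1 - ρ): -0.116, -0.077, -0.039 SD.
- 90% vs 10%: 0.8 × 0.348 / (0.27 + 0.07) = 0.818. Times (1 - ρ): -0.245, -0.164, -0.082 SD.

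**Simulation of the paired t test** (at least 2,000 runs per setting; ranges are across repeated runs). The last three columns give the share of null studies with a significant improvement; the nominal value is 2.5%.

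| Retested, abnormal vs normal | ρ = 0.7 | ρ = 0.8 | ρ = 0.9 |
|---|---|---|---|
| 50% vs 50% | about 2-3% | about 2-3% | about 2-3% |
| 70% vs 50% | 12-13% | 9-10% | 6-7% |
| 80% vs 30% | 61-62% | 44-46% | 25% |
| 90% vs 10% | 98-99% | 92-93% | 63-68% |

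**Fewer baseline values.** At 80% vs 30% and ρ = 0.8, false improvement falls from about 45% with 500 baseline values to 25-27% with 250 and 12% with 100. The bias stays near -0.077 SD.

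**Labs abnormal in both directions.** With 30% abnormal split equally between the two tails, 90% vs 10% retested and ρ = 0.8, the mean shift is 0.00 SD and false improvement 2-3%.

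**Likelihood analysis of everyone with a baseline value.** In the settings of the table, bias falls to within about 0.002 SD and false improvement returns to 2-3%.

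**Employer labs.** Suppose only patients tested at both ends are compared, with clinic patients retested at 90% vs 10%, comparison patients at 70% vs 50%, and ρ = 0.7. The spurious group difference is -0.245 - (-0.037) = -0.208 SD. Applying the same inclusion rule to both groups does not remove the bias when retesting habits differ.

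**The case against.** The best case on the other side has several parts.

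- **The size is unknown.** The article gives no retest rates, abnormal shares or correlations, and the clinic's testing routine is not shown. If nearly everyone is retested, or retesting ignores the first result, there is no bias. This stands: the bias is conditional. That labs arise only from usual care is also an inference from the wording, though the natural one.
- **Remedies are already in the plan.** HLM and the matched employer-lab comparison are both there. This stands in part. HLM is assigned to patterns and determinants while the paired test is named the main comparison, and the controlled analysis reaches only patients with employer lab data.
- **Not every lab is exposed.** TSH and the anemia measures can be abnormal either way, and shifts may cancel fully or in part. This stands. The composite scores were not simulated, so the single-lab figures should not be carried over to them.
- **Low consequence.** Labs are secondary. This stands.
- **The abstraction window.** Which result within months 6 to 12 counts as the 12-month value is operational detail that an abstraction manual or SAP may settle. It is not pressed here.

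A reader might infer that every lab outcome will falsely show benefit, or that the study's main conclusions are biased. The documents support neither. The first needs retest behavior that the article does not report. The second fails because quality of life and total cost do not depend on lab retesting.

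**Conclusion.** The concern holds as a conditional one. Taken together, chart-sourced labs, a paired test as main comparison and no control group leave these secondary outcomes open to a bias that would usually flatter the clinic and that the lead analysis could not detect. Under the stated assumptions the spurious change lies between about -0.01 and -0.25 SD, and false improvement between 6% and 99% of null studies. The upper end needs the most extreme retest contrast examined, and equal retesting gives none. The false-positive rates assume 500 baseline values and fall with fewer; the bias does not. The point applies mainly to labs abnormal in one direction.

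**What to change.** 1. For chart labs, name the already planned HLM as the main analysis. Fit it by likelihood to every patient with a baseline value, retested or not, with the baseline as one of the modeled outcomes so that patients with a single value are kept. Keep the paired t and McNemar tests as supportive.
2. Report the share retested separately for baseline-normal and baseline-abnormal patients.
3. Describe uncontrolled chart-lab changes as descriptive, not as clinic effects.
4. Where employer labs exist, compare the matched groups with a model that likewise includes all patients with a baseline value. Do not restrict the comparison to patients tested in both periods.
5. Reconcile the sections on whether chart data include a baseline, since the model needs one.

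The cost is a change of analysis wording and one extra table; no additional tests are needed. The limits are that the model corrects only for selection on the observed baseline, so retesting driven by unrecorded factors would still bias the result, and that the lab claim becomes more modest.

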The fifth analysis will focus on the subset of patients for which health insurance claims data are available and will utilize a matched comparison design. Prior to analysis all claims data for each individual (treatment and comparison groups) will be aggregated (by summation) into per health plan member per month (PMPM) totals of paid amounts (the amount paid by the health plan to the practitioner) for each of the following cost categories: total, inpatient, outpatient, emergency room, physician, and pharmaceutical claims. Similarly, the numbers of outpatient visits, hospital stays and emergency department visits will also be aggregated for each individual. The primary outcome will be total cost. Two comparison groups from de-identified claims data will be created—one using simple matching (e.g., by age and gender) and one using propensity scores [49]. After the comparison groups have been selected, simple descriptive analyses will show average PMPM costs and healthcare utilization (including standard deviations and other measures of dispersion) pre- and post- enrollment (or an equivalent date for the comparison groups) by gender, age, baseline diagnosis and by treatment and comparison group. Because cost data tends to be highly skewed, average PMPM costs and healthcare utilization pre/post enrollment, and the change in costs and utilization pre/post between the treatment and each of the comparison groups will be reported as mean differences with confidence intervals calculated using bootstrap methods [83,84]. Because of the number of data points for each patient (e.g., up to 12 PMPM values pre-enrollment and 12 post-enrollment), HLM [80-82] will be used to estimate the pattern of change in healthcare utilization and costs over time, and to explore the determinants of those patterns. Fidelity measures with significant changes over time [24], demographics, participants’ membership level and baseline diagnoses will be included as covariates in these models. Finally, changes in costs between groups will be compared to changes in patients’ CVD risk.

Results for the last two analyses will be reported following the Strengthening the Reporting of Observational Studies in Epidemiology (STROBE) guidelines [85]. For all outcomes, the estimated treatment effects will be reported using their original outcome scale and including confidence intervals.

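### Composite cardiovascular and metabolic scores are taken from the chart first and calculated otherwise, so a change of source between time points could appear as a change in risk

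*Protocol article*

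**What the plan says.** The protocol article, under Data collected from medical records, lists three composites: "10-year cardiovascular disease (CVD) event risk [70], 10-year CVD mortality risk [71], and metabolic syndrome diagnosis [72". Each carries one literature reference. The source rule for all three is that they "will be captured from the chart when recorded, or will be calculated", so a charted value comes first and calculation fills the gaps. The same form abstracts blood pressure, waist, weight, smoking status, use of glucose-, lipid- and blood-pressure-lowering drugs, and the results of listed laboratory tests, including fasting glucose, lipids and HbA1c.

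Under Analysis, the fourth analysis sets the main contrast: "The main comparison will be baseline to 12-month outcomes". It uses paired t tests or the McNemar test, plus hierarchical linear models. It then states: "These same analyses will be applied to other secondary outcomes such as CVD event [70] and mortality [71] risk". The fifth analysis closes with a further use: "Finally, changes in costs between groups will be compared to changes in" patients' CVD risk.

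Table 1 marks medical records data for pre/post comparison only. The section on comparison groups adds a matched comparison of key lab values where an employer holds them, but does not extend it to the composite scores.

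**The concern.** A paired contrast assumes that both values in a pair were measured in the same way. The source rule does not secure this. A patient may have a charted score at baseline and a calculated one at 12 months, or the reverse. If the two sources differ systematically and the mix shifts over the year, the difference enters the estimated change. No control group undergoes the same shift, so nothing subtracts it.

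The setting makes a shift plausible, though not certain. The Study design section describes a new clinic whose operational and treatment procedures are still being developed and modified, with fidelity results fed back to staff. Charting habits may change over the same period. The items listed for the fidelity chart extraction do not include risk-score recording, so the fidelity covariates would not obviously pick this up.

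At stake is the reading of two named secondary outcomes and of the closing comparison of cost change with CVD-risk change.

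**Working it through.** **No figure to reproduce.** The documents state no number that depends on the source rule. The check is therefore a reading of the text followed by an illustration on assumed inputs.

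**Reading the text**

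1. The charted value has priority for all three composites.
2. One reference per score indicates the intended definition. The text does not say that a charted value is accepted only if it was produced by that definition.
3. Nothing in the text ties a patient to one source across time points or has the source recorded.
4. The scores are analysed for within-person change with no concurrent control.
5. The baseline source is itself unclear. The medical-records section says "These data will be collected at 3, 6, and 12 months", and Table 1 agrees. The Data Collection section says "data will be collected from patient charts and self-reports at four intervals—baseline (initial clinic visit" and then the same three follow-up times. The two passages leave open how the starting value of each score is obtained.

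**Bias in the mean change**

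Let D be the mean difference between charted and calculated scores, and Δp the change in the share of patients with a charted score from baseline to 12 months. If D does not depend on who is charted:

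artefact = D × Δp

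Both inputs are assumptions:

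- D = 0 or Δp = 0: artefact 0
- D = 1 percentage point, Δp = 0.2: 1 × 0.2 = 0.2 points
- D = 3 percentage points, Δp = 0.6: 3 × 0.6 = 1.8 points

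The range is 0 to 1.8 percentage points of 10-year risk with no true change.

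**Effect on a nominal 5% paired test**

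Let a share s of patients switch source in one net direction, with an offset of b standard deviations of the change score, and let the true change be zero. Then:

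λ = s·b·√n / √(1 + s(1−s)b²)

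P(reject) = 1 − Φ(1.96 − λ) + Φ(−1.96 − λ)

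For s = 0.25, b = 0.2, n = 500: λ = 0.05 × 22.36 / √1.0075 = 1.11, and P = 0.20.

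| s | b | bias s·b (SD) | P(reject), n = 500 | P(reject), n = 200 |
|---|---|---|---|---|
| 0 | any | 0 | 0.05 | 0.05 |
| 0.10 | 0.2 | 0.02 | 0.07 | 0.06 |
| 0.25 | 0.2 | 0.05 | 0.20 | 0.11 |
| 0.25 | 0.5 | 0.125 | 0.78 | 0.41 |

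The two sample sizes are the expected outcomes sample and the figure in the power statement. The article does not say how many patients will have CVD scores at both ends.

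**Balanced switching.** If equal numbers switch each way there is no bias, only added variance of s·b². With s = 0.25 and b = 0.5 the standard error rises by a factor of √(1 + 0.25 × 0.25) = √1.0625 = 1.03.

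**Binary composite.** For metabolic syndrome, a change of source can by itself produce a discordant pair, and the McNemar test uses only discordant pairs. This would happen, for example, if a diagnosis stayed on the chart while current values no longer met the criteria. The documents do not say whether it will.

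**The case against.** The strongest reply is that each composite has a single reference, so the natural reading is one defined score with two routes to it: copy it if that score is in the chart, compute it if not. With the same algorithm and inputs the routes agree and the bias is zero. This stands as evidence of intent. A reader might go further the other way and infer that clinicians will chart scores from whatever tool they prefer. No part of the article says so, and the point does not rest on it.

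A second reply is that acceptance rules for charted values and source flags belong in an abstraction manual or analysis plan, neither of which is shown. That is fair for the missing flag. The order of sources, however, is stated in the article, and it is that stated rule which can be improved.

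A third reply is that taking charted scores first may guard against missing data. Test results are abstracted only when a test was done, and no study laboratory schedule is given. Components may therefore be missing for many patients, and the cited definitions are not at hand to confirm that the abstracted items suffice. This also stands. It is why charted scores should remain as a fallback rather than be discarded, and why one cannot claim that only a few patients would be affected.

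Finally, the Analysis section names CVD event and mortality risk as secondary outcomes but does not name metabolic syndrome. That diagnosis comes in only through the general wording on other outcomes and Table 1.

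**Conclusion.** The point holds as a conditional one. The stated source rule permits a patient's two values to come from different sources, and the uncontrolled pre/post design would not remove any resulting shift. Bias requires both a systematic difference between sources and a net change in the mix. The documents establish neither, so size and direction are unknown and may be zero. The 0 to 1.8 points and the rejection rates above show what assumed inputs would imply; they are not estimates for this study.

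A reader might infer that any drift in charting will appear as a treatment effect, or that the study's conclusions are compromised. The documents do not support either. Drift without a difference between sources does no harm. The primary outcomes, total cost and the quality-of-life scores derived from the SF-12, do not use these composites. The consequence is limited to secondary outcomes and to the one comparison of cost change with CVD-risk change. It is worth correcting because the remedy is simple.

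**What to change.** Reverse the order of sources. Calculate each composite by its cited definition from the abstracted components at every time point where they are available, baseline included, and record for each value whether it was calculated or charted. Use a charted score only as a flagged fallback when components are missing. Add a sensitivity analysis limited to patients whose score has the same source at baseline and 12 months. State where the baseline components come from, so that the medical-records section, Table 1 and the Data Collection section agree.

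The cost is a short calculation script and one source field on the abstraction form. Some patients will lack components and depend on the fallback. Their number cannot be judged from the article, so it should be reported by time point. The same-source analysis will be smaller and may be a selected group, which is why it is a sensitivity analysis and not the main comparison.
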